#### Inclusion criteria

3.2.1

(1) Age ≥ 60 years.(2) Scheduled for elective open or laparoscopic radical resection of gastric or colorectal cancer.(3) American Society of Anesthesiologists (ASA) physical status I-III.(4) Ability to provide written informed consent (or through a legal representative).

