#### Exclusion criteria

3.2.2

(1) Preexisting cognitive impairment (Montreal Cognitive Assessment score below education-adjusted cutoff) or diagnosed dementia.(2) Severe visual/hearing impairment or language barrier precluding reliable delirium assessment.(3) Major psychiatric disorders (e.g., schizophrenia, bipolar disorder).(4) Contraindications to SGB: local infection at the puncture site, known allergy to local anesthetics, severe coagulopathy, or therapeutic anticoagulation that cannot be safely paused.(5) Severe systemic disease: Child-Pugh C liver cirrhosis, end-stage renal disease (eGFR <30 mL/min/1.73 m^2^ or on dialysis), NYHA class III-IV heart failure.(6) Emergency surgery, anticipated surgery duration <2 h or >6 h.(7) History of substance abuse.

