### Randomization and blinding

3.3

Participants will be randomized in a 1:1 ratio to the SGB or sham group using computer- generated, permuted block randomization (block sizes of 4 and 6). Allocation will be concealed using sequentially numbered, opaque, sealed envelopes (SNOSE) prepared by an independent statistician. The envelope will be opened only by the research nurse preparing the study syringe.

This study is double-blind with respect to participants and outcome assessors. Participants, surgeons, postoperative care teams, and outcome assessors will be unaware of group allocation. The anesthesiologist performing the block will not be blinded due to the potential physical signs of a successful block (e.g., Horner’s syndrome) but will have no role in postoperative assessments or data collection.

Although successful SGB may produce visible signs such as Horner’s syndrome (ptosis, miosis, anhidrosis), these signs are typically ipsilateral and may be noticeable to the participant and potentially to the assessor. To evaluate the success of blinding, the following measures will be implemented:

(1) Participant blinding assessment: Within 24 h after the final postoperative delirium assessment, participants will be asked to guess their group assignment (SGB/sham/uncertain). The proportion of correct guesses will be compared between groups using a chi-square test to assess whether blinding was maintained.(2) Assessor blinding assessment: Outcome assessors will be asked to document any suspicion of group allocation (and the reason, e.g., observed Horner’s syndrome) after completing each participant’s delirium assessments. The frequency of suspected unblinding will be reported.(3) Mitigation strategies: To minimize unblinding, assessors will be instructed to avoid direct eye contact focused on the participant’s pupillary status and to focus on standardized assessment procedures. Participants will be instructed not to discuss any periprocedural sensations (e.g., facial warmth, ptosis) with assessors.

Results of the blinding effectiveness assessment will be reported alongside the primary outcome as a secondary analysis.

Unblinding will be permissible only in the event of a serious adverse event where knowledge of the intervention is crucial for clinical management. The unblinding procedure will be overseen by the principal investigator.

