#### Control of confounding variables

3.6.4

To minimize the potential impact of confounding variables on the primary outcome (POD incidence), the following measures will be implemented:

(1) Standardized perioperative management: As described in sections 3.5.1–3.5.3, all patients (both groups) will receive identical anesthesia, analgesia, and delirium prevention protocols. Any deviation from these protocols will be recorded as a protocol deviation.(2) Data collection on potential confounders: The following predefined variables, known to influence POD risk, will be collected and adjusted for in the statistical analysis: age, sex, body mass index (BMI), ASA physical status, baseline MoCA score, duration of surgery, intraoperative blood loss, intraoperative use of vasopressors, and postoperative opioid consumption (MME).(3) Statistical adjustment: In addition to the primary intention-to-treat analysis, a multivariable logistic regression model will be used to adjust for the above confounders, reporting adjusted odds ratios (aOR) with 95% confidence intervals.(4) Sensitivity analysis: A sensitivity analysis excluding patients with major protocol deviations (e.g., those who did not receive the allocated block, or those with incomplete primary outcome data) will be performed to assess the robustness of the findings.

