#### Analysis of primary outcomes

3.9.2

The cumulative incidence of POD on postoperative days 1–3 will be compared between groups using the Chi-square test, and relative risk (RR) with a 95% confidence interval (CI) will be reported. A supplementary multivariable logistic regression will be performed to adjust for pre-specified covariates: age, baseline MoCA score, and ASA physical status. To obtain adjusted relative risk instead of odds ratio, modified Poisson regression with robust standard errors will be adopted for covariate-adjusted analysis. Multivariable logistic regression will be used only as a supplementary approach when convergence issues occur.

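### Planned surgical approach and tumour site, both fixed at eligibility, are in neither covariate list and not used for stratification; the cost is modest precision and exposure to chance imbalance, not bias

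*Protocol article*

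**What the plan says.** - **Eligibility (3.2.1).** Patients are "Scheduled for elective open or laparoscopic radical resection of gastric or colorectal cancer". This admits four combinations of approach and site, and the planned one is known at screening. Section 3.2.2 narrows the case mix by excluding "Emergency surgery, anticipated surgery duration <2 h or >6 h".
- **Randomization (3.3).** Allocation is 1:1 in permuted blocks of 4 and 6. No stratification factor is named.
- **Primary outcome (3.9.2).** The main comparison is an unadjusted chi-square test with a relative risk. The supplementary adjusted analysis, by modified Poisson regression, will "adjust for pre-specified covariates: age, baseline MoCA score, and ASA physical status".
- **Confounders (3.6.4).** A second, longer list has the patient variables "age, sex, body mass index (BMI), ASA physical status, baseline MoCA score", then "duration of surgery, intraoperative blood loss, intraoperative use of vasopressors" and postoperative opioid consumption. The protocol describes this list as "known to influence POD risk, will be collected and adjusted for in the statistical analysis".
- **Secondary outcomes (3.9.3).** QoR-15 and length of stay are compared by t-test or Mann-Whitney test. The mixed models for pain and biomarkers contain group, time and their interaction. The opioid model adjusts for baseline pain, operation duration and body weight.
- **Timing (3.4.1).** The blocks are given on the afternoon before surgery and 30 min before induction.

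**The concern.** By listing duration and blood loss, the protocol itself treats the size of the operation as relevant to POD. Every measure of it that the plan uses arises after the blocks. The intervention could affect such variables, so adjusting for them may remove part of the treatment effect, and they do not replace a baseline factor. The two surgical facts that are fixed before allocation, planned approach and site, are used nowhere.

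They are plausible predictors of POD, and also of pain, opioid need, inflammatory response and hospital stay. If they do predict these outcomes, leaving them out gives up some precision, and a chance imbalance in, say, open surgery has no proper baseline correction in any planned model. The protocol concedes in 3.8 that the trial may be underpowered, so cheap precision has some value.

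**Working it through.** **Inputs from the protocol.** POD 40% (sham) and 20% (SGB), two-sided alpha 0.05, power 80%, 78 per group, 87 per group after 10% dropout (3.8).

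**Assumed inputs.** The protocol gives neither the share of open surgery nor the prognostic strength of approach or site. I take the prevalence *q* of one binary factor as 30-50% and its odds ratio for POD as 1.5 to 3.

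**1. The plan's own figure.** *n* = (1.96 + 0.8416)² × (0.4×0.6 + 0.2×0.8) / 0.2² = 7.849 × 0.40 / 0.04 = 78.5, which the plan takes as 78. Then 78/0.9 = 86.7, so 87 per group and 174 in total. The figure reproduces.

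**2. Chance imbalance, 87 per arm.** SD = √(2*q*(1−*q*)/87).
- *q* = 30%: √(0.42/87) = 0.0695. P(difference ≥ 10 points) = 15.0%; P(≥ 15 points) = 3.1%.
- *q* = 50%: √(0.50/87) = 0.0758. P(≥ 10 points) = 18.7%; P(≥ 15 points) = 4.8%.

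**3. Shift and gain for POD.** Stratum risks are solved so that the overall risks stay at 40% and 20%. The shift for a 10-point imbalance is 0.10 times the mean over arms of (risk with factor − risk without). The unadjusted variance term is 0.40. The adjusted one is the stratum-weighted sum of *p*(1−*p*) over both arms plus *q*(1−*q*)(*d*₁−*d*₀)²/2, where *d* is the stratum risk difference. Power uses 78 evaluable per group; unadjusted, 0.2/√(0.40/78) = 2.793, and Φ(2.793 − 1.96) = 79.8%.

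| *q* | OR | Sham risk without/with | SGB risk without/with | Shift, points | Effective N gain | Adjusted power |
|---|---|---|---|---|---|---|
| 30% | 1.5 | 0.370/0.469 | 0.180/0.247 | 0.8 | 0.7% | 80.0% |
| 30% | 2 | 0.349/0.518 | 0.165/0.283 | 1.4 | 2.2% | 80.6% |
| 30% | 3 | 0.320/0.586 | 0.143/0.333 | 2.3 | 5.8% | 81.9% |
| 50% | 1.5 | 0.352/0.448 | 0.168/0.232 | 0.8 | 0.8% | 80.1% |
| 50% | 2 | 0.318/0.482 | 0.146/0.254 | 1.4 | 2.4% | 80.7% |
| 50% | 3 | 0.272/0.528 | 0.117/0.283 | 2.1 | 5.9% | 82.0% |

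For scale, the standard error of the risk difference is √(0.40/78) = 7.2 points.

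**4. Continuous outcomes.** If approach shifts an outcome by *d* within-approach SDs, its share of variance is *q*(1−*q*)*d*² / (1 + *q*(1−*q*)*d*²). For *d* = 0.5 to 1.0 this is 5-17% at *q* = 30% and 6-20% at *q* = 50%. These values of *d* are also assumed.

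**5. Room in the POD model.** Expected events are 78 × 0.4 + 78 × 0.2 = 46.8, about 47. Group, age, MoCA and ASA I-III (two terms) take five parameters. Two more make seven, or 47/7 = 6.7 events per parameter.

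**The case against.** The strongest reply is that nothing here is wrong. The primary test is an unadjusted comparison under randomization and is valid whatever the covariate list holds. Age, MoCA and ASA are a defensible baseline set. The limits on anticipated duration already narrow the case mix, and duration and blood loss carry some information on surgical magnitude. The model has few events, and 3.9.2 already foresees convergence problems. All of this stands, and it limits the point to an improvement in precision.

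A reader might infer that a main source of variation has been left uncontrolled, or that every outcome is at risk of bias. The documents do not support either. They give no prognostic figure for approach or site, randomization balances both in expectation, and the opioid model does hold a surgical term, though a post-block one. Large imbalances are also uncommon: 15 points or more occurs in about 3-5% of trials.

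It is also fair to object that adding two main effects to the existing models would miss part of the target. The t-tests and Mann-Whitney tests take no covariates. In the mixed models, the group-by-time interaction is a within-patient contrast. With complete, balanced data and a random intercept, a term constant within patient cancels from it, so only the overall group comparison gains. The fix has to allow for both.

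The point does not depend on an unseen analysis plan. The article sets out the two covariate lists explicitly, and the comment concerns what they contain.

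**Conclusion.** The point holds as a small, inexpensive improvement. Planned approach and tumour site are baseline factors fixed at eligibility, absent from both covariate lists and from randomization, while post-block variables represent surgical magnitude.

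The type I error of the primary test is unaffected. For POD, a 10-point imbalance would move the estimate by well under half a standard error, and adjustment for one such factor would raise power by no more than about 2 points. The case may be stronger for continuous outcomes, but only if approach or site affects them by 0.5 SD or more. All sizes rest on the assumed prevalence and prognostic strength; only the sample size, event rates and timing come from the protocol.

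**What to change.** 1. **3.9.2:** add planned approach (open/laparoscopic) and site (gastric/colorectal) to the adjusted modified Poisson model. Define both as recorded at eligibility, not as performed, because a conversion happens after the block.
2. **3.6.4:** use these two factors instead of the post-block surgical variables, and bring the list into line with 3.9.2.
3. **3.9.3, opioid model:** use them instead of operation duration.
4. **3.9.3, mixed models:** include them, with time interactions where trajectories are compared.
5. **3.9.3, QoR-15 and length of stay:** report a covariate-adjusted linear model, suitably transformed if the outcome is skewed.

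Randomization need not change. The cost is revised wording, two fields known at screening, and two more terms in a POD model with about 47 expected events. Dropping the post-block terms offsets this in the 3.6.4 model. Section 3.1.1 reports no one enrolled at submission; if the change is made before outcome data are seen, it can still be properly pre-specified.

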#### Analysis of secondary outcomes

3.9.3

Continuous secondary outcomes measured at a single time point (e.g., total QoR-15 score on postoperative day 3, length of hospital stay) will be compared between groups using independent Student’s t-tests if data are normally distributed, or Mann–Whitney *U* tests if the normality assumption is violated. Normality will be assessed using the Shapiro–Wilk test and homoscedasticity using Levene’s test.

For longitudinal data collected at multiple time points (e.g., serial pain NRS scores every 8 h for 48 h, inflammatory biomarkers on POD1 and POD3), we will employ linear mixed-effects models with a random intercept for each patient to account for within-subject correlation. Fixed effects will include treatment group, time, and their interaction term. A significant interaction term would indicate different trajectories of change between groups.

Total opioid consumption over the first 48 postoperative hours (in morphine milligram equivalents, MME) is a count variable and will be analyzed using Poisson regression or negative binomial regression if overdispersion is present. Results will be expressed as incidence rate ratios (IRRs) with 95% confidence intervals. Overdispersion will be verified via Pearson chi-square divided by degrees of freedom. Baseline pain score, operation duration and body weight will be adjusted in regression models. Model fitness will be evaluated by AIC and deviance.

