### Sample size calculation

3.8

Based on prior literature reporting POD incidences ranging from 35 to 48% (2–4), we adopted a best-case scenario assumption for sample size planning: a baseline incidence of 40% in the sham group and a 50% relative risk reduction (to 20%) in the SGB group. Under these assumptions (*α* = 0.05, power = 80%, two-sided Chi-square test), 78 patients per group are required. Accounting for an estimated 10% dropout rate, the final sample size is 174 participants (87 per group).

We acknowledge that this effect size may be optimistic, especially given that our protocol excludes patients with preexisting cognitive impairment and includes a multicomponent delirium prevention bundle. If the true effect is smaller, this study may be underpowered for the primary outcome. Therefore, the results should be interpreted as hypothesis-generating, and future meta-analyses will be needed to confirm smaller effects.

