#### Statistical significance and software

3.9.5

A two-sided *p*-value <0.05 will be considered significant for the primary outcome. The false discovery rate (FDR) for secondary outcomes will be controlled using the Benjamini-Hochberg procedure. Analyses will be performed using SPSS 26.0 and R 4.3.2.

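### A Shapiro-Wilk pre-test on the trial's own data chooses between t-test and Mann-Whitney, so what is compared for QoR-15 on day 3 is not fixed in advance

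*Protocol article*

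**What the plan says.** Section 3.9.3 of the protocol article covers continuous secondary outcomes recorded at one time point, with two examples: "e.g., total QoR-15 score on postoperative day 3, length of hospital stay". These "will be compared between groups using independent Student’s t-tests if data are normally distributed"; the alternative is Mann-Whitney U "tests if the normality assumption is violated". The deciding test is named: "Normality will be assessed using the Shapiro–Wilk test and homoscedasticity using" Levene's test.

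The section gives no level for Shapiro-Wilk. It does not say whether the test is run in each arm, on the pooled data or on residuals. No other section fixes a single test for these outcomes.

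Two other sections bear on the point. Section 3.9.5 puts the outcomes in a multiplicity family: "The false discovery rate (FDR) for secondary outcomes will be controlled using the Benjamini-Hochberg procedure". Section 3.9.4 handles missing data by chained-equation multiple imputation with 50 datasets, combined by Rubin's rules.

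**The concern.** A t-test compares means. Mann-Whitney compares the chance that a patient in one arm scores higher than a patient in the other. These are different questions, and in skewed data they can have different answers. Under the stated rule, the observed data decide which question is asked of QoR-15.

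The pre-test is also a poor guide to the choice. With about 80 to 90 patients per arm, Shapiro-Wilk often rejects for mild skew that does little harm to a comparison of means. It also rejects at its nominal rate when the data are exactly normal.

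There is a practical clash with section 3.9.4. Rubin's rules combine an estimate and its standard error across imputed datasets. A mean difference supplies both; a bare Mann-Whitney result supplies neither. If QoR-15 is imputed, the pre-test could also select different tests in different imputed datasets.

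**Working it through.** **Sample size per arm.** Section 3.8 assumes "a baseline incidence of 40% in the sham group and a 50% relative risk reduction (to 20%) in the SGB group" and concludes "power = 80%, two-sided Chi-square test), 78 patients per group are required". The unpooled two-proportion formula reproduces this:

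n = (1.960 + 0.842)² × (0.40×0.60 + 0.20×0.80) / 0.20² = 7.849 × 0.40 / 0.04 = 78.49, against the stated 78.

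With 10% dropout, 78 / 0.9 = 86.7, so 87 per arm and 174 in total, as stated. The range for the pre-test is therefore 78 to 87 per arm.

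**Assumptions the article does not supply.** Shapiro-Wilk is run at 5% in each arm, and Mann-Whitney is used if either arm rejects. The outcome shapes are also assumed: Beta distributions, scaled for QoR-15, and log-normal for length of stay.

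**Exactly normal data.** The chance that at least one of two 5% tests rejects is 1 − 0.95² = 0.0975. Simulation gave 10% at 78 per arm and 11% at 87.

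**Other shapes.** Simulated share of trials sent to Mann-Whitney, with no group difference. Beta skewness is 2(b − a)√(a + b + 1) / [(a + b + 2)√(ab)].

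| Assumed shape | Skewness | Per arm | Sent to Mann-Whitney |
|---|---|---|---|
| QoR-15, Beta(10,5) | −0.33 | 87 | 38% |
| QoR-15, Beta(6,3) | −0.41 | 87 | 64% |
| QoR-15, Beta(8,3) | −0.54 | 87 | 83% |
| QoR-15, Beta(12,4), whole points | −0.53 | 78 / 87 | 71% / 77% |
| QoR-15, Beta(16,4) | −0.62 | 78 / 87 | 82% / 86% |
| Stay, log-normal, median 10 days, log-SD 0.2 to 0.6, whole days | right-skewed | 78 to 87 | at least 99.6% |

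Check on one row: for Beta(16,4) at 87 per arm, a single arm rejects in 63.9% of trials, and 1 − (1 − 0.639)² = 0.87, against 0.864 simulated.

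**Type I error.** The two-stage procedure rejected in 0.046 to 0.056 of null trials (3000 per scenario). The simulation standard error is √(0.05 × 0.95 / 3000) = 0.004, so this range is compatible with 0.05. A separate run gave 0.043 to 0.059.

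**Does the branch change the call?** The t-test and Mann-Whitney disagreed on significance in about 2% to 5% of null trials, and in 2.0% to 2.4% for the Beta(12,4) and Beta(16,4) shapes.

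**Levene.** With n per arm, the pooled standard error is √[((s₁² + s₂²)/2) × (2/n)] = √[(s₁² + s₂²)/n]. This is the Welch standard error, so at 1:1 allocation the two t statistics are identical and only the degrees of freedom differ.

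**The case against.** The rule is written in advance and limits the analyst's discretion. It touches secondary outcomes only, and the primary chi-square comparison is unaffected. The authors already call their results hypothesis-generating. All of that stands and keeps the point small.

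The switching rates rest on choices the article does not make. A single test on residuals at 5% would switch in about 5% of trials with normal data, not 10%, and the figures for skewed data follow the shape assumed. That also stands. But the article's silence on how the test is run leaves the branch less determined, not more.

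Four stronger readings are tempting and are not supported:

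- A reader might infer that the pre-test inflates type I error or spoils the p-values entering the Benjamini-Hochberg procedure. The simulated error stays near 0.05, and no damage to that step is shown.
- A reader might infer that length of stay is equally left to chance. If stay is skewed as assumed, the rule picks Mann-Whitney almost always.
- A reader might infer that only the t-test can give an effect in points or days. A Hodges-Lehmann difference does so on the rank side. The article names no effect measure for either branch, and that detail may properly sit in an analysis plan not shown here.
- A reader might see the lack of any stated consequence of Levene's test as a serious gap. With equal allocation little depends on it.

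**Conclusion.** The point holds as a minor one. It concerns a rule the protocol article states, not a detail left to another document. For QoR-15 on day 3, whether means or ranks are compared is settled by a pre-test on the trial data. At 87 per arm, switching if either arm rejects at 5%, Mann-Whitney is reached in about 10% of trials under exact normality and about 38% to 83% under the three main left-skewed shapes; two further assumed shapes reach 86%. These shares depend on assumed distributions and on an assumed way of running Shapiro-Wilk.

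The consequence is an estimand not fixed in advance. Where QoR-15 values are imputed, there is also a rank result that cannot be combined by Rubin's rules as it stands. Error control is not materially affected.

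**What to change.** In section 3.9.3, remove Shapiro-Wilk and Levene as rules for choosing a test, and name one method and one effect measure per outcome:

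- QoR-15 on day 3: Welch t-test, mean difference with 95% CI, whatever the distribution looks like. This estimate pools directly under section 3.9.4.
- Length of stay: Wilcoxon rank-sum, Hodges-Lehmann difference with 95% CI. This is the test the current rule would almost always reach if stay is skewed, now with an effect in days.
- Any other continuous outcome at a single time point: one stated default, since the article lists these two only as examples.

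The cost is wording in the protocol and in any analysis plan, and one analysis in place of two branches. QoR-15 may lose a little efficiency if scores are strongly skewed. Section 3.1.1 reports no enrolment at submission, so the change counts as pre-specified if made before outcome data are seen.

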### Outcome measures

3.7

A summary of the assessment schedule is provided in Table 1 (SPIRIT).

**Table 1 tab1:** SPIRIT schedule of enrolment, interventions, and assessments (23).

Study period	Enrolment	Intervention		Postoperative period (daily: POD1-3)	Close-out
Timepoint	≤7 d pre-op	Day-1 p.m.	Day 0	POD1-3	D/C
Enrolment					
Eligibility screen	X				
Informed consent	X				
Interventions					
SGB/Sham block		X	X		
Surgery and standardized care			X		
Data collection					
Demographics, medical history	X				
MoCA	X				
ASA physical status	X				
Outcome measures					
Primary outcome					
POD incidence (3D-CAM)				X (POD1-3 bid)^a^	
Secondary outcomes					
Delirium severity (MDAS)^b^				X (POD1-3 bid)^b^	X (record)
Quality of recovery-15 (QoR-15)				X (on POD3)	
Inflammatory biomarkers (procalcitonin, CRP, IL-6, LMR, NLR)^c^	X (blood)			X (on POD1 and POD3)^c^	
Postop pain intensity (NRS)^d^				X (q8h, POD1-2)^d^	
Opioid consumption (MME)^d^				X (total, POD1-2)^d^	
Postop complications (Clavien-Dindo)^e^				X (daily)^e^	X (record)
Length of hospital stay (days)					X
Safety monitoring					
Adverse events (AEs)		X	X	X (daily)	X

a POD incidence (3D-CAM): assessed twice daily (bid) from postoperative day 1 to day 3.

b Delirium severity score: assessed daily (POD1-3). Total delirium duration is recorded at discharge (D/C).

c Inflammatory biomarkers: blood samples collected at baseline (V0), postoperative day 1, and postoperative day 3.

d Postop pain and opioid use: pain intensity (NRS) is assessed every 8 h (q8h) for the first 48 h only (POD1-2). Total opioid consumption (MME) is calculated and recorded for the first 48 h (POD1-2).

e Postop complications: monitored daily (POD1-7) and recorded at discharge.

D/C, discharge; SGB, stellate ganglion block; MoCA, Montreal Cognitive Assessment; ASA, American Society of Anesthesiologists; POD, postoperative day; 3D-CAM, 3-Minute Diagnostic Interview for CAM-defined Delirium; QoR-15, quality of recovery-15 scale; CRP, C-reactive protein; IL-6, interleukin-6; NRS, numerical rating scale; MME, morphine milligram equivalents; bid, twice daily; q8h, every 8 h.

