#### Secondary outcomes

3.7.2

(1) Delirium severity, assessed using the Memorial Delirium Assessment Scale (MDAS), and total delirium duration (number of days with a positive 3D-CAM assessment).(2) Quality of recovery- 15 (QoR-15) score on postoperative day 3.(3) Plasma levels of inflammatory biomarkers (procalcitonin, C-reactive protein, interleukin-6, lymphocyte-to-monocyte ratio [LMR], neutrophil-to-lymphocyte ratio [NLR]) at baseline, postoperative day 1, and postoperative day 3.(4) Postoperative pain intensity (NRS) trajectories and total opioid consumption (morphine milligram equivalents) over 48 h.(5) Incidence of postoperative complications (Clavien-Dindo classification) and length of hospital stay.

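### Secondary-outcome models omit the collected biomarker baseline, call opioid MME a count and adjust it for an unscheduled pain score; the random-intercept model also puts the serial pain interaction test at risk

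*Protocol article*

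**What the plan says.** Section 3.9.3 of the protocol article covers serial pain scores and inflammatory biomarkers with "linear mixed-effects models with a random intercept for each patient to account for within-subject correlation". The mean structure of these models is then set out as follows: "Fixed effects will include treatment group, time, and their interaction term". The only term it interprets is the last: "A significant interaction term would indicate different trajectories of change between groups". It does not say whether time is linear or categorical.

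For the biomarkers it names "inflammatory biomarkers on POD1 and POD3", whereas section 3.7.2 defines the outcome "at baseline, postoperative day 1, and postoperative day 3" and Table 1 (note c) schedules all three samples.

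Total 48-hour MME "is a count variable and will be analyzed using Poisson regression or negative binomial regression if overdispersion is present", with a Pearson check for overdispersion and results as incidence rate ratios. In that paragraph, "Baseline pain score, operation duration and body weight will be adjusted in regression models". Table 1, note d, says "pain intensity (NRS) is assessed every 8 h (q8h) for the first 48 h only (POD1-2"), and the table marks no pain score at enrolment, on the day before surgery or on the day of surgery.

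**The concern.** The mechanistic and analgesic conclusions will come from these models.

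- **Biomarkers.** A baseline value that is drawn but left out gives away precision and protection against chance imbalance. With only two post-block times, a benefit of equal size on both days does not appear in the one term the plan interprets.
- **MME.** Treating a dose as a count ties the choice of model to the unit of measurement and mislabels the estimate.
- **Baseline pain.** A covariate with no scheduled measurement invites a substitute. The obvious one, the first postoperative score, is taken after the block and may be changed by it.
- **Serial pain.** A random intercept forces the same correlation between scores 8 hours apart and 40 hours apart. If nearer scores are more alike, the interaction test can reject too often.

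**Working it through.** The plan states no figure to reproduce here. Correlations, SDs, MME means and coefficients of variation (CV) below are assumptions, because the protocol gives none. Sample sizes are from section 3.8: 78 per group before dropout, 87 after.

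**1. Biomarkers.** Collected: baseline, day 1, day 3. Modelled: days 1 and 3, with group, time and interaction.

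- Residual variance after baseline adjustment is multiplied by 1 − ρ². At ρ = 0.3 this is 0.91 (a 9% cut); at ρ = 0.6 it is 0.64 (a 36% cut).
- With two times, the interaction is the day 3 group difference minus the day 1 group difference. If both equal δ, it is δ − δ = 0.
- Illustration: δ = 0.4 SD, 78 per arm, between-day correlation 0.4 to 0.6. The SE of the averaged difference is √(2 × [(1 + ρ)/2] / 78), which is 0.134 to 0.143. Then z = 0.4/SE = 2.99 to 2.79, and power is 85% to 80%. The interaction test rejects 5% of the time, its nominal level.
- Type I error of that interaction test, simulated with 87 per arm and 10,000 replicates in nine scenarios (ρ 0.2 to 0.8, day 3 to day 1 SD ratio 1 to 0.25), was 0.047 to 0.052. With two balanced times it equals a t-test on change scores, so there is no inflation.
- With baseline entered as a third time instead, type I error was 0.049 to 0.065 (categorical time) and 0.055 down to 0.001 (linear time).

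**2. MME.** Section 3.6.2 builds the amount from a weight-based solution in mg/kg, a continuous infusion and rescue doses in mg. Nothing is counted.

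- Pearson dispersion is about SD²/mean. With mean 60 and SD 30 it is 900/60 = 15. In a unit one third the size, mean 180 and SD 90 give 8100/180 = 45.
- Equivalently it is CV² × mean. At CV 0.3, mean 60 gives 5.4. The same data in a unit ten times larger (mean 6) give 0.54, and the switch no longer occurs.
- Simulated gamma-distributed MME, no true effect, 87 per arm, 3,000 replicates:

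| Setting | Dispersion | Plain Poisson type I error | With planned switch |
|---|---|---|---|
| Mean 60–120, CV 0.3–0.7 | about 5–58 | 0.39–0.79 | 0.043–0.060 |
| Mean 6, CV 0.3 | 0.54 | 0.008 | 0.008 (no switch) |

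**3. Baseline pain.** Section 3.9.3 requires the score. Table 1 and its note d place every pain score after surgery. As scheduled, the covariate does not exist.

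**4. Serial pain.** 48 h / 8 h = about six scores. Type I error of the group-by-time test from a random-intercept model, no true effect, 87 per arm, 10,000 replicates, nominal 0.05 (simulation error about √(0.05 × 0.95/10,000) = 0.002):

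| True correlation | Categorical time | Linear time |
|---|---|---|
| Equal, 0.5 | 0.054 | 0.050 |
| AR(1) 0.3 | 0.056 | 0.104 |
| AR(1) 0.5 | 0.066 | 0.156 |
| AR(1) 0.7 | 0.075 | 0.210 |
| AR(1) 0.85 | 0.081 | 0.237 |
| Random slopes, SD 0.1–0.3 per 8 h | 0.051–0.060 | 0.067–0.159 |

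A separate run with 78 per arm and 4,000 replicates, at AR(1) 0.5, 0.7 and 0.85, gave 0.064, 0.073 and 0.085 (categorical) and 0.156, 0.202 and 0.243 (linear). A test on per-patient slopes, which uses the between-patient slope variance, gave about 0.06 at AR(1) 0.7 (200 replicates only), against 0.21 for the random-intercept test with linear time.

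**The case against.** The strongest reply is that much of this is detail for an analysis plan that is not shown, that only secondary outcomes are affected, and that the trial calls its results hypothesis-generating (section 3.8). Several parts of that reply stand.

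- **Interaction.** Section 3.9.3 lists group as a fixed effect and does not make the interaction the sole test. For pain, section 3.7.2 names trajectories as the outcome, so a trajectory test answers a declared question. A reader might infer that the trial would miss a constant effect. That follows only if the interaction is used as the decision rule, which the protocol does not say.
- **Biomarker times.** Days 1 and 3 appear in a parenthesis of examples. If baseline enters as a time point, a constant post-block effect does produce an interaction. The sections still disagree, and no baseline covariate is listed. Without baseline the randomised comparison remains unbiased.
- **MME.** The switch to negative binomial restores about 5% error at plausible values, and dispersions of 15 and 45 both trigger it. Under a log link the exponentiated coefficient is an interpretable ratio of means, so the fault is the label. A reader might infer that the opioid model cannot be fitted. Only the missing pain score obstructs it.
- **Baseline pain.** Table 1 is described as a summary, and the protocol does not propose a postoperative substitute. Even so, note d limits pain scoring to the first 48 postoperative hours, so this is a contradiction and not an omission.
- **Serial pain.** The larger figures need linear time, which the protocol does not state, and an assumed AR(1) pattern.

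The false discovery rate control in section 3.9.5 does not answer the pain point, because it takes valid p-values as its input.

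**Conclusion.** The point holds in limited form: three defects and one risk, all in secondary analyses. The primary analysis is untouched.

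1. The biomarker baseline is collected and unused in the stated model. The cost is precision (9 to 36% of variance at assumed correlations of 0.3 to 0.6) and exposure to chance imbalance.
2. MME is wrongly typed as a count. The consequences are a unit-dependent choice of model and a mislabelled estimate, not a material excess of false positives at plausible values.
3. The MME model needs a pain score that the schedule does not provide.
4. For serial pain only, the interaction test may be anti-conservative: about 6 to 8% with categorical time and 16 to 24% with linear time, under assumed AR(1) correlation of 0.5 to 0.85. If the true correlation is equal at all lags, there is no inflation.

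A reader might conclude that random-intercept models overstate interaction significance throughout. The documents do not support that: with the two biomarker times as written, the test keeps its 5% level.

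**What to change.** - **Biomarkers:** reconcile sections 3.7.2 and 3.9.3. Model the day 1 and day 3 values, on the log scale where skewed, adjusted for the baseline value. Report the group difference averaged over time and at each time, with the interaction as supportive.
- **MME:** remove the description as a count. Use a gamma model with log link and robust standard errors, reporting a ratio of means, or a linear model on log(MME), reporting a ratio of geometric means.
- **Baseline pain:** drop the covariate, or add one preoperative pain score to Table 1. Do not substitute a score taken after the block.
- **Serial pain:** state that time is categorical and use an unstructured or AR(1) residual covariance.

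The cost is analysis wording and at most one extra preoperative pain question. Section 3.1.1 reports that no participant had been enrolled at submission, so the wording could be settled before any data were seen.
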